### Statistical Methods

Baseline patient demographics will be presented as descriptive statistics. Primary outcome (rate of positive diagnostic tests) will be presented as descriptive statistics (percentage of positive tests) at all predefined time points.

Secondary outcomes include the association between subjective (questionnaire outcomes evaluating systemic symptoms or ASIA symptoms) and objective findings (MAT, blood test). For this outcome, subjective complaints are summed (each complaint is 1 point). Objective findings are dichotomized. The association between the number of subjective complaints and the presence of objective findings is subsequently calculated via Chi-Square Test or Fisher’s Exact Test in low expected counts, where applicable. For missing data, percentage of data present will be described. If known, a rationale for missing data will be presented. If only limited data is missing per variable, analysis will proceed as expected. Imputation of missing data is not preferred as imputation within the relatively small sample size would decrease validity of the study, as well as the intention to present real data as it is.

A p-value <0.05 is considered statistically significant. Success rates of (partial) mesh removal will be presented as descriptive statistics (percentage of successful surgery).

Patients are considered to have ASIA when either two major or one major and two minor criteria are present (adapted from Cohen Tervaert 2018) [17]. In the present study, we only considered patients to have ASIA when at least three major criteria are present.

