### Participants

Fifty consecutive patients with suspected systemic autoimmune/autoinflammatory response or ASIA syndrome will be recruited from one of the five aforementioned departments. In the present study, patients are considered to have ASIA when at least three major criteria from Table 1 are present, as previously published [17]. Only referrals from the outpatient ASIA clinics will be accepted and no active recruitment will be undertaken. Subjects will be eligible for inclusion if they meet all of the following criteria:- Patients >18 years of age and written informed consent obtained;- Suspected ASIA syndrome after elective inguinal hernia, POP, or SUI repair, defined as at least three major ASIA criteria (Table 1), of which the exposure to an external stimulus (PP mesh) is one;- ASIA complaints started specifically after the implantation of PP mesh and were not present before the surgical repair.

**TABLE 1 T1:** Diagnostic criteria autoimmune/autoinflammatory syndrome induced by adjuvants (ASIA) syndrome [17].

Major criteria
- Removal of inciting agent induces improvement
- Exposure to an external stimulus (infection, vaccine, silicone, adjuvant) prior to clinical manifestations
- The appearance of ‘typical’ clinical manifestations:
- Myalgia, myositis or muscle weakness
- Arthralgia and/or arthritis
- Chronic fatigue, unrefreshing sleep or sleep disturbances
- Neurological manifestations (especially associated with demyelination)
- Cognitive impairment, memory loss
- Pyrexia
- Sicca (dry mouth and/or dry eyes)
- Typical biopsy of involved organs
Minor criteria
- The appearance of autoantibodies or antibodies directed at the suspected adjuvant
- Other clinical manifestations (e.g., irritable bowel syndrome)
- Specific HLA (e.g., HLA DRB1, HLA DQB1)
- Evolvement of an autoimmune disease (e.g., multiple sclerosis, systemic sclerosis)

Patients will be excluded from participation in this study if one or more of the following is present:- Known autoimmune/inflammatory disorders;- Known malignancies;- (Low grade) infections or other inflammatory diseases at time of surgery;- Cognitively impaired individuals.- Recent (<3 months) vaccination

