Sample size calculation is not applicable as the present study is a pilot and preceding literature about the validity of MAT is absent, but considering the low expected number of cases annually, with strict inclusion criteria (at least 3 major ASIA criteria present), and no active recruitment in only three centres, total number of proposed inclusions has been estimated restrictively, in order not to misjudge availability of inclusions.

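### The complaint score is an ordered count, but the named chi-square or Fisher test ignores its order and loses power that 50 patients can ill afford

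*Protocol article*

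**What the plan says.** The Statistical Methods section of the protocol article builds the two variables in consecutive sentences: "subjective complaints are summed (each complaint is 1 point). Objective findings are dichotomized". It then names the test: "The association between the number of subjective complaints and the presence of objective findings is subsequently calculated via Chi-Square Test", with Fisher's exact test as the fallback for low expected counts, where applicable. The threshold is also given: "A p-value <0.05 is considered statistically significant".

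The section mentions no rank or trend test, and no grouping or cut-point for the count. It names no other hypothesis test: the rate of positive tests (the primary outcome) and the success rate of mesh removal are descriptive.

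Under Participants, "Fifty consecutive patients with suspected systemic autoimmune/autoinflammatory response or ASIA syndrome will be recruited", and the size is not based on power: "Sample size calculation is not applicable as the present study is a pilot". The number of complaints that can enter the sum is not stated. Table 1 lists seven typical clinical manifestations, and the text also refers to questionnaire outcomes without giving a number of items.

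**The concern.** A sum of complaints is ordered: a patient with six has more than a patient with three. A chi-square or Fisher test on the count by a yes/no finding gives the same p-value if the count levels are shuffled. It therefore spreads its sensitivity over every departure from independence, including patterns of little interest, such as only patients with exactly four complaints differing. The question of interest is whether patients with a positive finding have more complaints.

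This is not a detail left to an analysis plan. The article names the test, and the test does not suit the variable defined just before it. At stake is the sensitivity of the only named hypothesis test, in a sample that is already small.

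**Working it through.** **Inputs from the article.** n = 50; significance level 0.05, taken as two-sided; a count with no stated grouping; a binary finding; chi-square or Fisher. There is no power figure to reproduce.

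**Assumed inputs.** Number of count levels, MAT-positive rate and effect size. Seven manifestations scored 0 to 7 would give eight levels; a range of 2 to 7 would give six.

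**Step 1: which test would be used on the full count.** With six equally likely levels, each holds 50/6 = 8.3 patients on average. Expected counts in the MAT-positive row are 8.3 × 0.2 = 1.7, 8.3 × 0.3 = 2.5 and 8.3 × 0.5 = 4.2. All are below 5. In every simulated table with the full count, more than 20% of cells had an expected count below 5, so the unordered exact test would apply.

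**Step 2: analytic bound.** A one-degree-of-freedom trend test with a given power has noncentrality λ = (z(0.975) + z(power))². For 80% power, λ = (1.960 + 0.842)² = 7.85; for 50%, λ = 1.960² = 3.84. The unordered test on k levels places the same λ on k − 1 degrees of freedom.

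| Levels k | Power if trend has 80% | Relative loss | Power if trend has 50% | Relative loss |
|---|---|---|---|---|
| 3 | 71% | 11% | 40% | 20% |
| 6 | 56% | 31% | 28% | 44% |
| 8 | 49% | 38% | 24% | 52% |
| 16 | 36% | 56% | 17% | 65% |

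**Step 3: simulation, six levels.** A latent normal score is cut into six levels, equally likely in MAT-negative patients, with a 0.8 SD shift in positives.

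| MAT-positive | Chi-square | Unordered exact | Median split, Fisher | Rank-sum | Loss, unordered exact | Loss, median split |
|---|---|---|---|---|---|---|
| 20% | 25% | 24% | 37% | 53% | 1 − 24/53 = 55% | 1 − 37/53 = 30% |
| 30% | 34% | 35% | 45% | 64% | 1 − 35/64 = 45% | 1 − 45/64 = 30% |
| 50% | 43% | 43% | 51% | 73% | 1 − 43/73 = 41% | 1 − 51/73 = 30% |

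An independent repeat gave chi-square 24/33/44%, rank-sum 52/64/73% and median split 35/45/50%. Extending the same model to eight levels (2,500 trials per rate, 1,000 for the exact test, tie-corrected rank-sum) gave rank-sum 54/67/73% against unordered exact 18/28/40%, losses of 67%, 59% and 45%.

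**Step 4: a different data model.** Item-level responses, baseline item probability 0.45, ordered comparator a linear trend test (rank-sum power at most about 0.06 lower).

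- 7 items, 30% positive, log odds ratio 0.75 per item: trend 0.71; chi-square 0.39; Fisher 0.41. A median split gives 0.57 (chi-square) or 0.50 (Fisher), a loss of 20% to 30%.
- 7 items, 50% positive, log odds ratio 0.75: trend 0.78; chi-square 0.39; Fisher 0.43.
- 15 items, 20% positive, log odds ratio 0.5: trend 0.48; chi-square 0.14; Fisher 0.15. A median split with Fisher gives 0.29, a loss of 38%.

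**Step 5: where the loss shrinks.** In the model of step 3 with three levels, it is about 16% to 26%. With six levels and a 1.2 SD shift, it is about 13% to 38%. In the item-level model with log odds ratio 1.5, 7 items and 30% positive, the planned test has 0.945 against 0.998, a loss of about 5%.

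**Type I error.** It was about nominal (0.02 to 0.06) for all tests.

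**The case against.** The strongest case against has four parts.

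- **The size is not fixed by the document.** Number of items, grouping, positivity rate and effect size are all unstated. This stands: any single figure is conditional. A reader might infer that the plan loses half its power as a matter of fact. The documents do not support that, because the loss runs from about 5% to about 70% over plausible settings.
- **The count may be grouped in the full protocol.** This is possible, and the uncollapsed table is an assumption. Grouping into two still loses about 25% to 40% for moderate effects, and grouping into three about 16% to 26%, so the point is reduced but not removed.
- **The analysis is secondary, in an exploratory pilot with no power claim.** This stands and limits the weight of the point. A reader might also infer that a real association will probably be reported as absent. That rests on one assumed effect: a large effect would be found by either test, and at 20% positivity the rank-sum test itself reaches only 53%.
- **The rank-sum test is favoured by simulating a shift.** This is fair. It is less sensitive to non-monotone patterns, so the change is not free of any cost. A shift is, however, the pattern that a summed complaint score is built to show.

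The absence of an effect estimate is not counted against the article, since an analysis plan may supply it.

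**Conclusion.** The point holds as one of efficiency, not validity. The article fixes a test that ignores the ordering of the variable it has just defined.

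For the full count at six to eight levels, a 0.8 SD shift and 20% to 50% positivity, power is roughly 40% to 60% lower than with a rank-sum test, and up to about two-thirds lower at eight levels and 20% positivity. A median split costs about 25% to 40%. Three levels or a very large effect bring the loss to about 5% to 25%; a 1.2 SD shift at six levels lies between. All of these rest on assumed inputs.

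The direction does not depend on them: the ordered test had the higher power in every scenario with an effect. The same applies to the blood findings. Type I error is intact and the primary outcome is untouched.

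**What to change.** Replace the test sentence in Statistical Methods. Compare the complaint count between finding-positive and finding-negative patients with an exact Wilcoxon rank-sum test that allows for ties, for MAT and for each prespecified blood finding. Report the probability that a positive patient has more complaints than a negative one (ties counted as half), or the Hodges-Lehmann difference, with a 95% confidence interval. The probability is the easier to read for a short count with many ties. Keep Fisher's exact test for two-by-two tables only.

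State in the same place which complaints enter the sum, so that the range of the count is known.

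The cost is a sentence or two, with no new data and no extra patients. The one small loss is lower sensitivity to non-monotone patterns, which a descriptive table of the count by finding would still show.

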## Discussion

To our knowledge, this study is the first to date to prospectively evaluate the difficulties and unknowns in pragmatic diagnosis, natural progression, and quality of life of ASIA-afflicted patients after PP implantation. Due to concerns within society regarding PP implants being a safety hazard, physicians are left with an unresolved problem as scientific literature is scarce. Therefore, it is likely to result in unnecessary diagnostics and high healthcare costs without any proven benefit to the patient. Prospective studies on the causal relation between adjuvants and ASIA are limited, and lacking regarding PP. Furthermore, medical treatment is currently targeted unequivocally at completely removing the adjuvant, or reducing a generalized immune response, with proof of its effectiveness consisting predominantly of selected case reports and case series [23–25]. This pilot is the first step to systematically examine patients with possible PP-associated ASIA and their complaints in relation to time, objective blood and screening tests, (effectiveness of) operative treatment, and self-reported complaints via validated questionnaires. Without this evidence, caution is warranted in supporting unproved and potentially unsafe treatments leading to redundant or excessive (re-)operations [26–28].

A series of studies have been published on the relationship between adjuvants that can cause inflammation and their possible relation to autoimmune diseases or ASIA. Most of these studies offer either a hypothetical pathophysiological basis for symptoms [19, 29], or describe a series of vastly varying cases with heterogeneous triggers for the immune response [17, 20, 30]. Systematically obtained proof of correlation between PP implants and ASIA remains to be published [31]. Kowalik et al. (2021) performed a systematic review and found little literature on an association between PP and ASIA [23]. Furthermore, they found no evidence of a correlation between PP and systemic autoimmune syndromes [23]. A second systematic review, performed by Jisova et al. (2023) found that multiple studies show no clear evidence linking PP implantation to ASIA. Studies reporting evidence of autoimmunity after mesh implantation were accompanied by high risk of bias, insufficient reporting of confounders, and absence of relevant distinction between autoinflammation and chronic foreign body reaction. Both reviews included the retrospective cohort study of Chughtai et al. (2017), which investigated the onset of autoimmune diseases after interventions. The paper included colonoscopy patients as a control group and used exact individual matching for comparison [22]. Chughtai found no difference in incidence of autoimmune disease between the colonoscopy group (1.6%; n = 25,432) and PP group (1.5%; n = 12,716) after an average of 6 years follow-up [22]. In the present pilot study, patients are prospectively included and are comprehensively tested during the study period. Patients who are not included in the group that undergo surgical removal of the prosthesis could function as a naturalistic control group to those patients that received surgical removal. Considering included patients undergo similar exposure, blood sample collection and follow-up data retrieval, this might lead to potential future analytical strategies. We aspire to provide stronger evidence to base future correlational analysis on and subsequently lead to evidence-based practice for physicians that treat these patients.

This pilot aims to assess the diagnostic value of Mesh Allergy Testing as a first objective screening tool, to aid physicians in decision-making for possible treatments (including high-risk mesh removal) [26, 27]. MAT has not been validated as a test for screening systemic reaction to an adjuvant before, necessitating the current exploratory nature of this study. While findings in physical examination and medical history can aid in a differential diagnosis, testing patients for susceptible HLA-types or antibodies related to mesh has unknown predictive values. Currently, only subjective patient or observer described diagnostic modalities are considered in the ASIA criteria, leading to a lack of specificity in discerning patients with ASIA from other syndromes (Table 1) [17]. The current pilot therefore intentionally opposes earlier case series on ASIA by only including patients with at least three major ASIA criteria, to form a narrower but more specific patient population. Consequently, to assess the value of MAT, patients who suffer from light ASIA symptoms or who only slightly match the diagnosis, will be excluded to create a homogeneous population of patients who fit the criteria of ASIA most optimally, to test value of MAT [32]. In addition, patients will be referred to an immunologist to test for identifiable autoimmune diseases and relevant confounders, and to exclude other illnesses that could correctly explain the presented symptoms.

In our pilot, the explanted meshes will all be sent for histopathologic examination to identify ongoing microscopic inflammatory processes and to relate these to potentially positive MAT results, despite earlier research by Fadaee et al. (2019) showing minor to no benefits of this test as proof of any relation between PP and ASIA [33]. Additionally, while presence of (chronic) inflammation, foreign body reaction, and fibrosis surrounding the mesh explant are to be expected, reports of pathology findings can lead to a deeper understanding of the difference between autoimmunity and (normal) foreign body reactions in patients suffering from ASIA [33]. Objective diagnostic modalities for ASIA are essential, and a rapid, low-cost, non-invasive diagnostic test such as MAT could be a vast improvement in the diagnosis of patients; if results are promising and consistent [32].

Whilst the existence of ASIA has not yet been solidified, it is vital that physicians take patients presenting with these complaints seriously [34, 35], as other mechanisms may (also) underlay these complaints. A stubborn fear amongst patients exists that medical specialists receive funding from professional organizations and industries, to hide the true damage of suggested treatments [12, 13, 36–39]. This is particularly true for patients who have developed complaints after PP mesh implantation as a considerable number visit numerous specialists and charlatans with expensive and ineffective treatments [11]. The misunderstanding of physicians may lead to fear, and sometimes anger aimed at the surgeon who implanted the PP prosthesis. This makes it difficult to construct a trustful bond between patient and physician, although essential for optimal treatment results. For these patients it is essential for the physician to undertake effort to grow trust, to abstain from expressing any derogative comments, and to level with the patient and their insecurities. As the earned trust is fickle and delicate, taking a comprehensive anamnesis is vital and emphasis should be put on the complaints of the patient and their impact. The onset of symptoms in relation to the PP implantation, and presence of pain, may give further clues for diagnosis. When signs of immune activation are present, it is highly recommended to rule out other known autoimmune disorders. Surgeons should be hesitant to ‘blindly’ perform surgical removal of the implant, considering risks for necessary follow-up surgery [28, 40]. Considering the large number of PP implants placed globally every year, it is striking that there is still so little literature on the existence of ASIA after PP implantation [41]. Until research yields higher quality evidence of the causal relationship between PP implants and autoimmunity, future perspectives for patients suffering from ASIA are grim, as misinformation, misunderstanding, and misguidance of patients will remain.

### Limitations

MAT is used to test for type IV allergic reactions as a possible underlying mechanism for systemic complaints. There is no literature regarding this mechanism so far, and the effectiveness and meaning of the MAT for ASIA patients is uncertain. The proportion of patients that present with all symptoms supporting presence of ASIA as stated by Shoenfeld’s criteria, but with a negative MAT is yet to be deduced [17]. Furthermore, as this pilot is not a clinical trial and treatment is not randomized, it is likely that patients with complaints will opt for surgical removal of the PP implant, making it increasingly difficult to illustrate the normal progression of ASIA symptoms. Note should be taken that the effectivity of surgical removal is not the primary aim of this pilot! The natural course of complaints of ASIA patients will be displayed for future studies to further base new standards of care on.

## Conclusion

As the use of PP implants for hernia, SUI and POP repair is successful in the vast majority of patients; surgeons, (uro)gynaecologists and urologists wish to continue these mesh-based techniques to have optimal results and to prevent recurrences. Taking available literature into consideration, the incidence of PP-based ASIA symptoms is probably very low. No causal relation between PP mesh and development of autoimmune syndromes has been demonstrated to date, and considering the substantial risk of co-morbidity of surgical mesh removal, surgeons should be hesitant to operate these patients for this indication. Until the present study has been carried out, physicians should be cautious to suggest that PP implants cause autoimmune syndromes. These suggestions can distress patients, shifting patients’ preference to operative interventions without proper indication and potentially harm them. Furthermore, patients who experience ASIA symptoms and attribute these to their mesh placement, will often seek treatments that are not (yet) supported by evidence. This could lead to more harm than benefit when not meeting their predefined expectations, increasing their distrust in healthcare in general [42, 43]. Instead, physicians should discuss with these patients that the available evidence does not indicate a causal association between PP implants and autoimmune syndromes. When patients present with symptoms indicating excessive immune activation, the treating physician should exclude other autoimmune diseases before applying the ASIA diagnostic criteria. Currently, patients suffering from ASIA-like complaints are doomed to a lack of understanding from their peers and scarce information and treatment from professionals, due to insubstantial evidence that corroborates any association between polypropylene mesh implants and their complaints. The present study will aim towards new evidence-based insights for diagnosis and treatment of these patients.

## Data Availability

The raw data supporting the conclusions of this article will be made available by the authors, without undue reservation.
